## Abstract

**Background:**

The urban environment plays a significant role in shaping residents’ health, wellbeing, and opportunities for social participation. Urban development interventions have been shown to positively influence physical activity, mental health, quality of life, and self-reported health status. However, most previous studies have focused on single measures or specific environmental aspects. Integrated Urban Development Plans (IUDPs), by contrast, combine interventions from multiple domains, such as housing, infrastructure, green spaces, and social participation, to promote health equity and sustainable urban transformation. The SalusTransform project aims to evaluate IUDPs in three German cities regarding their implementation processes as well as their impacts on health, social equity, and ecological sustainability.

**Methods:**

We will compare three IUDP intervention areas with three control areas in the respective cities using a mixed-methods design. Quantitative and qualitative data will be collected to assess both process and outcome quality of the IUDPs. Primary data collections include resident surveys and focus groups, qualitative interviews with stakeholders, as well as environmental and infrastructural assessments, including air-quality measurements, site visits, and observations related to active mobility and urban green spaces. Secondary data on population structure, aggregated health indicators, and local implementation processes will be provided by the municipalities. Analyses will follow a difference-in-differences approach to identify changes attributable to IUDP implementation while accounting for similar developments in the control areas.

**Discussion:**

By building a comprehensive database that links health-related, social, and environmental indicators, SalusTransform will provide valuable evidence on the real-world effects of IUDPs. Findings will inform municipalities, policymakers, and practitioners about the effectiveness and transferability of IUDPs and contribute to the institutionalisation of their systematic evaluation. Close collaboration with local authorities will ensure continuous monitoring of changes and strengthen the practical relevance of the research. Targeted communication strategies will be implemented to engage population groups that are often underrepresented in research and urban planning processes.

**Trial registration:**

This study was prospectively registered with the German Clinical Trials Register (DRKS00036042) on May 28th, 2025.

**Supplementary Information:**

The online version contains supplementary material available at 10.1186/s12889-026-28247-7.

## Background

The urban environment plays a significant role in shaping health and wellbeing. With an estimated 75% of the global population expected to live in cities by 2050, urban development and urban planning are becoming more and more critical topics for addressing complex public health challenges [1, 2]. Cities concentrate both opportunities and risks: while they may provide access to healthcare, education, employment, and cultural resources, they are also sites where air pollution, limited green space, traffic-related hazards, and social stressors converge [3, 4]. Due to their diverse socioeconomic structures, in cities health inequities are particularly present and need to be considered when urban development measures are conceptualised and implemented [5].

Urban development interventions especially aim to address problems in disadvantaged neighbourhoods. Existing research has demonstrated that urban development interventions can have positive effects on residents’ health and well-being. Studies and reviews have reported improvements in outcomes such as physical activity, mental health, and perceived health status. These positive effects followed interventions targeting specific aspects of the built or social environment. Examples include the external and internal upgrading of private homes, the improvement of (path) infrastructure, and the redesign of public (green) spaces. Such measures were often complemented by interventions aimed at social interaction, such as offering shared neighbourhood activities or establishing local political bodies to involve residents [6–12]. However, most studies have focused on single or narrowly defined measures rather than comprehensive, multi-component strategies. Evidence on the combined or synergistic effects of integrated urban interventions – comprehensively addressing dimensions of the natural, built and social environment at the same time – remains limited.

To combine and integrate various types of interventions while considering the interconnectedness of different domains of action and the need for cross-sectoral collaboration, Integrated Urban Development Plans (IUDPs) are developed in Germany [13]. As informal, integrative instruments of urban development, IUDPs play a particularly important role in improving urban living conditions in neighbourhoods facing multiple challenges. Based on preparatory analyses, municipalities first identify sub-areas that are structurally, economically, and socially disadvantaged and derive thematic priorities accordingly. These priorities encompass health-relevant determinants such as access to green and public spaces, barrier-free infrastructure, or healthcare provision. Although IUDPs are always developed for a specific urban context and involve various municipal departments and public participation for concept development, they follow a comparable logic and often employ similar interventions. IUDPs describe both a process and a bundle of measures through which various stakeholders aim to steer the development of a city or district in a desired direction. They serve as overarching strategies that initiate additional activities and measures in a given urban area, even when financed through separate funding sources. With their diverse urban renewal measures, IUDPs are an example of complex interventions implemented in an urban setting [14–16]. They meet the criteria for complex interventions as defined by Skivington et al. [17].

Up to now, there is a lack of comprehensive evaluations of IUDPs that analyse real-world impacts on health, equity, and sustainability of neighbourhoods. Thus, the project SalusTransform will include both process and outcome evaluations and aims to assess how IUDPs are implemented and whether they improve the social determinants of health of the built, natural and social neighbourhood environment as well as residents’ quality of life, to promote greater health equity. We will collect quantitative and qualitative data using a mixed methods approach and employ participatory data collection methods. We will not implement any interventions by ourselves.

## Methods

### Study setting

This study will evaluate the impact and process quality of IUDPs in three urban areas in Germany. The intervention areas are the districts of Blumenthal (I1) in the city of Bremen, federal state of Bremen in northern Germany, Wattenscheid-Mitte (I2) in Bochum and Mirke (I3) in Wuppertal, both cities located in the federal state of North Rhine-Westphalia in the western part of Germany. In each city, a further district will serve as control area in which no IUDP will be implemented. These control areas are Bremen Kirchhuchting (C1), Bochum Hofstede (C2) and Wuppertal Rott (C3). For the localisation of all six study areas within Germany and the respective cities, see Fig. 1.

**Fig. 1 Fig1:**
[figure not shown]
Localisation of the six study areas within Germany and the respective cities

The study protocol is reported and implemented according to the Standard Protocol Items: Recommendations for Interventional Trials (SPIRIT) Statement (see Additional file 1 for the checklist).

### Description of study areas and IUDPs

The three intervention areas and the three control areas are located in three different cities in Germany, with populations ranging from 360,000 (Wuppertal) to 585,000 (Bremen) inhabitants [18]. All study areas have a similar population structure across various social indicators and face comparable challenges concerning population characteristics, infrastructure and environmental conditions. Further details about the population characteristics of the six study areas are presented in Table 1.

**Table 1 Tab1:** Population characteristics of the intervention and control areas

	**Bremen Blumenthal**^**a**^	**Bremen Kirchhuchting**^**b**^	**Bremen** **total**	**Bochum** **Wattenscheid**^**a**^	**Bochum Hofstede**^**b**^	**Bochum total**	**Wuppertal Mirke**^**a**^	**Wuppertal Rott**^**b**^	**Wuppertal total**
Population	10,706	9,356	586,271	23,309	10,341	375,204	8,573	10,188	358,200
Proportion of migrants^c^	57.1%	61.9%	43.5%	46.0%	44.4%	34.9%	59.9%	52.2%	42.6%
Proportion of foreigners^d^	34.7%	32.3%	22.9%	27.2%	22.6%	17.0%	38.2%	31.5%	23.0%
Unemployment rate	22.0%	19.0%	12.6%	12.2%	9.5%	7.4%	10.8%	10.0%	10.9%
Proportion of unemployment assistance^e^	29.7%	25.9%	16.2%	25.8%	18.2%	14.1%	24.0%	23.9%	15.5%
Age structure									
≥ 65 years	16.5%	18.4%	20.6%	26.4%^f^	26.6%^f^	29.3%^f^	11.8%	16.0%	20.6%
< 18 years	23.6%	22.5%	17.1%	17.9%	22.3%	15.2%	18.9%	19.5%	14.1%
Old-age dependency ratio^g^	27.6%	31.1%	33.1%	n. a	n. a	n. a	14.6%	19.0%	35.2%
Youth dependency ratio^h^	39.4%	38.1%	27.5%	n. a	n. a	n. a	27.0%	30.2%	33.7%

^a^Intervention area

^b^Control area

^c^Migrants: Non-German nationals and naturalized Germans, and German children < 18 with at least one parent with a migration background

^d^Foreigners (% of migrants): Individuals without German citizenship

^e^Proportion of residents under 65 receiving unemployment benefits (basic income support)

^f^Owing to methodological differences in data collection in Bochum, this age group includes individuals aged ≥ 60 years rather than ≥ 65 years

^g^number of people aged 65 + divided by the working-age population (15–64), multiplied by 100

^h^number of people aged 0–14 divided by the working-age population (15–64), multiplied by 100

IUDPs, as complex interventions, are developed over a multi-year process, adopted by municipal political committees, and then gradually refined and implemented over several years. This extended development and implementation phase lasts often six years or more. For SalusTransform, we selected three IUDP areas that differ in terms of their stage of IUDP implementation to be able to capture various aspects of implementation, outputs, outcomes and impacts (see Fig. 2).

**Fig. 2 Fig2:**
[figure not shown]
Timeline of the three Integrated Urban Development Plans (IUDPs)

In I1, the IUDP was approved by the Senate in April 2023, and the first measures were implemented at the end of 2023.

In I2, the implementation of IUDP measures, financed through the initial urban development funding, began in 2015. The second phase of urban development funding was commenced in early 2025, providing further financial resources for the implementation of additional measures.

In I3, the implementation of measures from a preceding IUDP began as early as 2007. With the update to the current extension in 2014, additional funding was made available, allowing further development of the area. The final measures will have been funded in 2026.

### Primary data collection methods

Following a mixed-methods approach, we will employ multiple data collection strategies, including: (1) two cross-sectional surveys conducted in the six study areas; (2) qualitative interviews with representatives of the authorities responsible for the formal implementation of the IUDPs, as well as key local stakeholders involved in on-site intervention delivery; (3) focus groups with residents of the intervention areas; (4) assessments of physical activity and sleep using accelerometers; (5) participatory formats involving the residents in the interventions areas, and (6) environmental assessments, including on-site visits, observations of active mobility and urban green spaces, as well as air-quality measurements.

#### Surveys of the residents

We will conduct two surveys in the study areas, one in the first and the other in the third year of the project. The surveys will target residents aged 18 years and older living within the defined study areas. In Bremen and Wuppertal, all residents will receive a personal access code enabling them to complete the survey online. In Wattenscheid-Mitte, due to the substantially larger population, a random sample of residents will be invited to participate, with the number of invitations adjusted to achieve a sample size comparable to the other intervention areas. The survey will be implemented on LimeSurvey, an open-source online survey tool [19]. The survey will include a set of validated questionnaires: Warwick Edinburgh mental well-being scale [20], Short Scale Measuring Perceived Social Participation [21], Oslo-3-Items-Social-Support Scale [22], self-efficacy short scale [23], and Abbreviated Place Attachment Scale (APAS) [24]. We will also use items on general mental and physical health status from the German Federal Health Reporting surveys, provided by the Robert Koch Institute (RKI) [25]. Furthermore, we will collect information about the participants’ living and housing situation, their subjective assessment of their living environment concerning (1) traffic infrastructure, (2) impairments due to noise, air pollution, and other environmental threads, (3) the proximity and accessibility of public green spaces, as well as their perceived impact on and involvement in urban planning decisions affecting their living environment. We will provide translations of the questionnaire in the most common languages of the study areas.

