### Secondary data sources

In addition to primary data, we will collect secondary data from various sources provided by the respective city authorities. These data will include information on the population structure of the study areas (e.g. number of inhabitants, age distribution, proportion of residents with a migration background, unemployment rates, and other sociodemographic indicators), as well as aggregated health and environmental data. Health data will include indicators such as life expectancy, results from school entry examinations, and other aggregated public health statistics. Environmental data will include information on air and noise pollution, heat exposure, and the availability and quality of green spaces.

For the intervention areas, we will also gather detailed information on the IUDPs’ implementation processes from the responsible authorities, including data on expenditures, participation rates, and the use of specific interventions such as counselling services or small subsidy programmes for private homeowners. Additionally, we will document any delays in the implementation and their underlying causes. To ensure a longitudinal perspective, secondary data will be collected retrospectively for a period of ten years prior to the start of the respective IUDP and continuously throughout the project duration.

In the control areas, we will assess whether any interventions are planned or implemented that target similar dimensions as the IUDPs but have not been formally developed or approved as such. Close cooperation with local authorities and the wider network of practitioners in the study areas, established during the project conception phase, will ensure comprehensive and reliable access to these data sources.

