### Data analyses

To evaluate the effectiveness of IUDPs as complex interventions, the intervention areas will be compared with the control areas in regard to the aforementioned evaluation parameters. Regarding the IUDPs’ implementation, this includes an analysis of specific outputs, such as structural or socio-spatial changes in the neighbourhoods. In addition to the assessment of these outputs, we will focus on different outcome parameters in each city: in Bremen (I1, C1), these include Outcomes I and short-term Outcomes II; in Bochum (I2, C2), short- and long-term Outcomes II; and in Wuppertal (I3, C3), long-term Outcomes II and Impacts (Fig. 3).

Both bivariate and multivariate analyses will be conducted using established statistical procedures appropriate to the data structure. Quantitative data from the cross-sectional surveys at two time points, environmental data emerged from the different data collection formats, as well as secondary quantitative data collected at multiple time points, will be analysed using a difference-in-differences (DiD) approach [38]. Both absolute (difference-in-differences) and relative changes (ratio-of-ratios) will be assessed, and inequality effects will be examined through stratification by various social indicators [39]. From an intersectional perspective, social indicators will be selected based on the PROGRESS-Plus framework, as recommended by the Campbell and Cochrane Equity Methods Group [40]. The quantitative data analysis will be carried out using SAS (version 9.4 or higher) and R (version 4.5.1 or higher) [41].

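### The survey difference-in-differences can show only the change between project years 1 and 3 in areas already exposed to an IUDP, not the effect of the IUDP since its start

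*Protocol article*

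**What the plan says.** Primary data include "two cross-sectional surveys conducted in the six study areas" (Primary data collection methods). The section Surveys of the residents fixes their timing: "We will conduct two surveys in the study areas, one in the first and the other in the third year of the project". In the Abstract, the purpose of the analysis is given as follows: "Analyses will follow a difference-in-differences approach to identify changes attributable to IUDP implementation". Data analyses sets out to evaluate the effectiveness of the IUDPs and names DiD for the surveys, the environmental data and the secondary data together.

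Exposure dates are in Description of study areas and IUDPs. For Bochum: "In I2, the implementation of IUDP measures, financed through the initial urban development funding, began in 2015". On later funding for that area, the same section adds: "The second phase of urban development funding was commenced in early 2025". For Wuppertal, "the implementation of measures from a preceding IUDP began as early as 2007", with an extension in 2014 and the final measures funded in 2026. In Bremen the first measures date from the end of 2023.

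Data analyses sets the outcome level by city: short- and long-term Outcomes II in Bochum, and "in Wuppertal (I3, C3), long-term Outcomes II and Impacts (Fig. 3").

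Only the secondary data reach back before exposure: "secondary data will be collected retrospectively for a period of ten years prior to the start of the respective IUDP" (Secondary data sources).

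**The concern.** A two-wave DiD returns the full effect of a programme only if the first wave precedes the programme. In Bochum and Wuppertal the first wave comes a decade or more after the start, and in Bremen about two years after. By the protocol's own account, Bochum had already completed several measures, including two park redesigns, and Wuppertal has had two successive IUDPs. Whatever these had changed by wave 1 is part of the baseline and is subtracted.

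This matters most for well-being and self-rated health, for which the survey is the only quantitative source. The secondary data listed are population structure, aggregated health statistics such as life expectancy and school entry examinations, and environmental indicators. No later analysis choice can supply a pre-IUDP survey wave. Read as the wording invites, a small survey DiD in a late-stage area would be taken as a small IUDP effect, although the design cannot show most of that effect.

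**Working it through.** The plan gives no figure for this point, so there is none to reproduce.

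**Identity.** Let d(t) be the effect of the IUDP on the intervention-minus-control difference at time t, with a stable area difference A and parallel trends in the absence of the IUDP.

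DiD = [A + d(wave 2)] − [A + d(wave 1)] = d(wave 2) − d(wave 1)

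This equals the full effect d(wave 2) only if d(wave 1) = 0.

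**Inputs.**
- Starts, from Description of study areas and IUDPs: Bochum 2015 (second phase early 2025, taken as 2025.1); Wuppertal 2007 or 2014; Bremen end of 2023, taken as 2023.9.
- Survey dates are not stated. Assumed: wave 1 between 2025.5 and 2026.0, from the registration of May 2025, and wave 2 two years later (2027.5 to 2028.0).

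**Share of the wave-2 effect that the survey DiD can show, linear accrual.** Share = 2 / (wave 2 − start).

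| Area and start | Years exposed at wave 1 | Wave 2 at 2027.5 | Wave 2 at 2028.0 |
|---|---|---|---|
| Wuppertal, 2007 | 18.5 to 19.0 | 2/20.5 = 9.8% | 2/21.0 = 9.5% |
| Wuppertal, 2014 | 11.5 to 12.0 | 2/13.5 = 14.8% | 2/14.0 = 14.3% |
| Bochum, 2015 | 10.5 to 11.0 | 2/12.5 = 16.0% | 2/13.0 = 15.4% |
| Bochum, 2025 phase only | 0.4 to 0.9 | 2/2.4 = 83% | 2/2.9 = 69% |
| Bremen, end of 2023 | 1.6 to 2.1 | 2/3.6 = 56% | 2/4.1 = 49% |

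The row for the 2025 phase assumes that the effect of earlier Bochum measures no longer changes between the waves. If it does change, the survey DiD mixes the two phases.

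**Sensitivity to the shape of accrual.** With d(t) proportional to 1 − exp(−t/τ) and τ = 3, 5 or 10 years, the shares are 0.1-3% for Wuppertal from 2007, 1-8% for Wuppertal from 2014, 1-9% for Bochum from 2015 and 32-51% for Bremen. If linear accrual in Wuppertal stopped at the end of 2026, the shares would be 5-8% (from 2007) or 8-12% (from 2014).

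**Anchor of the secondary series.** Ten years before 2007 is 1997-2006; ten years before Bochum's start is 2005-2014. If the respective IUDP in Wuppertal were read as the 2014 plan, the ten years would be 2004-2013, of which 2007-2013 (7 of 10) are already exposed.

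**The case against.** The strongest reply is that the protocol promises to identify changes, not the accumulated effect since 2007 or 2015. The three areas were chosen openly because they are at different stages, and outcome levels are assigned by city, not by data source. The secondary series with ten pre-IUDP years is already planned, and nothing says that Wuppertal's Impacts must come from the surveys. Much of this stands. The survey DiD is not void: the increment between waves is estimable under parallel trends, and for Bochum's 2025 phase it may capture most of the effect.

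It does not remove the point. The text never says that the survey DiD is incremental, it dates Bochum's launch to 2015, and it analyses all sources by DiD under one statement about effectiveness.

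Some stronger readings are tempting but unsupported:
- That a successful IUDP must give a survey DiD near zero. This needs a plateau before wave 1, which the documents do not describe; funding in 2026 does not mean that measures or effects have ended.
- That the estimate will be negative. This needs the control area to catch up, for which there is no evidence.
- That the Wuppertal secondary series will be anchored on 2014. The wording is ambiguous, and 2014 is only one reading.
- That accelerometry shares the problem in Bochum and Wuppertal. It is planned only in the two Bremen areas.
- That procedural justice rests on the survey alone. Participation rates from the authorities, focus groups and participatory formats also inform it.

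**Conclusion.** The point holds in a limited form. Both survey waves follow the start of IUDP measures: by about 10 to 11 years in Bochum, 18 to 19 (or 11 to 12 from the extension) in Wuppertal, and about 2 in Bremen. The survey DiD therefore estimates incremental change between project years 1 and 3. Read as the effect of the IUDP since its start, it leaves out any effect already present at wave 1 and so understates a benefit that had built up by then.

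The shares are illustrative: they rest on the assumed survey dates and an assumed shape of accrual. The cancellation needs neither. Any project start near the 2025 registration puts wave 1 about a decade or more after the starts in Bochum and Wuppertal. Secondary series with a true pre-IUDP period are not affected.

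**What to change.** 1. In the Abstract and Data analyses, define the survey DiD estimand as the additional change between project years 1 and 3 in areas already exposed. Say for Bochum whether the target is the 2025 phase or the IUDP since 2015. State that a null survey result in Bochum or Wuppertal is not evidence of no IUDP effect.
2. Base claims on long-term Outcomes II and Impacts in Bochum and Wuppertal on the secondary series with pre-IUDP years. In Secondary data sources, state that for Wuppertal the start means the first IUDP (2007), so that 2007-2013 is not used as unexposed time. If earlier data cannot be obtained, say that no clean pre-period exists.
3. Report adjusted wave-1 differences between intervention and control areas as associations only.

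The cost is wording and a different choice of lead analysis for the long-term claims; the retrospective collection is already planned, though anchoring Wuppertal on 2007 calls for data back to 1997. The downside is weaker causal claims for survey outcomes in two of the three cities.
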